#### Sample Power for Simulated Trial

The primary hypothesis to be tested in this study focuses on the efficacy of ASSIST-ICU in making evidence-based guideline physical activity decisions in a simulated EHR environment compared to no decision support. We hypothesize that participants assigned to the ASSIST-ICU intervention group will achieve a higher proportion of decisions that meet the out-of-bed safety definition. Assuming a true mean of 4.5 correct decisions out of 6 simulations (75% probability) when using the decision tool and 3 correct decisions (50% probability) when not using it, 2-sample binomial test simulations show that 25 clinicians per group will provide 99.2% power when testing for a between-group difference at α=.05.

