### Phase 2: ASSIST-ICU Simulated Trial Design

#### Overview

We will conduct a simulated trial comparing the ASSIST-ICU CDSS interface with usual care (no ASSIST-ICU interface) in a simulated EHR environment. We will operationalize evidence-based decision-making through the creation of 6 expert-validated clinical scenarios. Of the 6 simulations, 3 will meet the out-of-bed safety definition, and 3 will not. All 6 simulations will be completed by each participant in a random order generated using the RAND function of Microsoft Excel. The decisions (regarding whether out-of-bed activity is safe or unsafe) will be recorded, and the number of correct decisions (range 0-6) for each participant will serve as our outcome measure of effectiveness (Table 2).

**Table 2 table2:** Operationalization for scoring each clinical scenario.

	ASSIST-ICU^a^ CDSS^b^ recommends patient out of bed: yes	ASSIST-ICU CDSS recommends patient out of bed: no
Clinician decision to mobilize patient out of bed: yes	1	0
Clinician decision to mobilize patient out of bed: no	0	1

^a^ASSIST-ICU: Aggregating Patient Safety and Status Information to Support Time-Sensitive Interventions in the Intensive Care Unit.

^b^CDSS: clinical decision support system.

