#### Study Participants for Simulated Trial

The inclusion criteria will be as follows: (1) licensed RN or PT, (2) at least 6 months of experience working in an ICU (to align with the advanced beginner stage of the Dreyfus model of skill acquisition [52,53]), (3) access to a tablet or computer for the design session, and (4) fluent in English. The exclusion criteria will be as follows: (1) no EHR experience in a critical care setting and (2) inability to use a cloud-based video platform.

We will recruit a sample of 50 licensed RNs and PTs (control group: n=25, 50%; intervention group: n=25, 50%) using publicly available lists from the professional state boards of 7 geographically diverse states. We will randomly select clinicians to contact. Using a modified version of the tailored design method proposed by Dillman et al [54], each selected clinician will be contacted using different modes (ie, letters, postcards, and email) up to 5 times in a 21-day cycle. For generalizability purposes, we will use a quota sampling methodology to ensure that the clinicians represent the demographics of the profession [50]. In addition to the random sample, up to 15 clinicians will be recruited using convenience sampling to assess the fidelity of ASSIST-ICU (eg, agreement between clinical scenario sequence and variable display in CDSS) in the simulated EHR.

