#### Data Collection and Analysis for Simulated Trial

Clinicians will receive a score ranging from 0 to 6 based on the number of scenarios answered correctly. Participants will complete 3 brief surveys using a hyperlink in the cloud-based video platform’s chat feature to assess the usability (System Usability Scale [SUS] [55]), cognitive workload (NASA-TLX [43]), and acceptability (Acceptability of Intervention Measure [AIM] [56]) of CDSS and decision-making process as a whole. The SUS is a 10-item Likert-type scale that is widely used to measure usability across a broad range of interfaces and performs well psychometrically (Cronbach α=0.70-0.92) [57,58]. The NASA-TLX is a 6-item scale that measures subjective cognitive workload in performing a specific task and is a reliable measure of cognitive workload across industries, including ICU clinicians (Cronbach α=0.83-0.92) [59]. The AIM is a 4-item Likert-type scale that measures acceptability and performs well psychometrically (Cronbach α=0.85-0.91).

Summary statistics will be calculated for the collected measures by group. Continuous measure distributions will be assessed for normality and reported as means and SDs or medians and IQRs, as appropriate. Categorical measures will be reported as counts and percentages for each level. A 2-sample binomial test will be used to test the null hypothesis that decision accuracy with the support tool does not differ from accuracy without it. Further between-group assessments will be conducted for SUS, NASA-TLX, and AIM scores using 2-sample 2-tailed *t* tests or the Wilcoxon rank sum test. *P* values will be reported based on 2-sided alternatives, and statistical significance will be evaluated at α=.05.

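### The simulated trial's primary test is a 2-sample binomial test although each clinician contributes six decisions, so the 99.2% power assumes no between-clinician variation and the 5% error rate is not assured

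*Protocol article*

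**What the plan says.** The article's section on participants for the simulated trial plans 50 clinicians, 25 per group. The Overview of the simulated trial says: "All 6 simulations will be completed by each participant in a random order". It defines the effectiveness outcome as each participant's count of correct decisions, from 0 to 6. Three scenarios meet the out-of-bed safety definition and three do not.

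The section Sample Power for Simulated Trial sets the alternative: "Assuming a true mean of 4.5 correct decisions out of 6 simulations (75% probability) when using the decision tool", against 3 of 6 (50%) without it. It then concludes: "2-sample binomial test simulations show that 25 clinicians per group will provide 99.2% power when testing for a between-group difference at α=.05".

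The section Data Collection and Analysis for Simulated Trial names the primary test: "A 2-sample binomial test will be used to test the null hypothesis that decision accuracy with the support tool does not differ". It reserves two-sample t tests or the Wilcoxon rank sum test for the usability, workload and acceptability scores. On error control it says "values will be reported based on 2-sided alternatives, and statistical significance will be evaluated at α=.05". Neither section mentions correlation between decisions of the same clinician, a design effect or a clinician term.

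**The concern.** The tool is given or withheld per clinician, so the clinician is the independent unit. A 2-sample binomial test compares two proportions built from independent yes/no observations. Here there are 25 clinicians per arm but six binary decisions from each. Followed as written, the test would treat one clinician's six decisions as if six different clinicians had made them.

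Clinicians may differ in skill: the sample mixes nurses and physical therapists with six months of ICU experience or more. If they do, the true variance of the arm proportion exceeds the binomial variance and the test rejects too often under the null. This is the test of the hypothesis that the article calls primary. Its Discussion uses the virtual trial to establish safety and effectiveness before real-world ICU testing, so the P value should mean what it says. The stated power rests on the same assumption.

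**Working it through.** **Inputs from the article:** 25 clinicians per arm; 6 decisions each; accuracy 0.50 against 0.75; two-sided α = 0.05. The number 150 is not printed; it is 25 × 6.

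**Step 1. Reproduce the stated power with the named test.** For n observations per arm, mean proportion 0.625 and the pooled z test:

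- SE under the null = √(2 × 0.625 × 0.375 / n); SE under the alternative = √((0.25 + 0.1875) / n)
- Power = Φ((0.25 − 1.96 × SE under the null) / SE under the alternative)
- n = 150: SEs are 0.0559 and 0.0540, so power = Φ((0.25 − 0.1096) / 0.0540) = Φ(2.60) = 99.5%
- n = 25: SEs are 0.1369 and 0.1323, so power = Φ((0.25 − 0.2684) / 0.1323) = Φ(−0.14) = 44%

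Exact enumeration gives 99.5% (pooled z) and 99.3% (continuity-corrected or Fisher) at n = 150. At n = 25 it gives 47.9% and 35.8%. With a binomial test, a figure near 99.2% therefore needs all 150 decisions per arm.

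**Step 2. Check whether a clinician-level test could also give 99.2%.** Scores were simulated as Binomial(6, 0.50) and Binomial(6, 0.75), 25 per arm, so that all clinicians in an arm share the same accuracy. The Wilcoxon test on the 0–6 scores gives about 99.2%, and the t test about 99.4%. The stated figure therefore does not by itself show which unit was used. Both routes set between-clinician variation to zero.

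**Step 3. Allow clinicians to differ.** The documents give no ICC; 0.05–0.30 is an assumption. The formulas are:

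- Design effect DE = 1 + (6 − 1) × ICC
- Effective decisions per arm = 150 / DE, put into the power formula of step 1
- Type I error of the pooled test = 2 × (1 − Φ(1.96 / √DE))

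Example, ICC 0.10: DE = 1.5, 100 effective decisions, power 96.0%, type I error 2 × (1 − Φ(1.60)) = 11.0%.

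The simulated columns use a beta-binomial model with skill differences only (20,000 runs).

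| ICC | DE | Pooled test type I error, formula | Same, simulated (p = 0.75 to 0.50) | Power, formula | Power, t test on scores, simulated |
|---|---|---|---|---|---|
| 0.05 | 1.25 | 8.0% | 8.1–9.0% | 98.3% | 97.7% |
| 0.10 | 1.50 | 11.0% | 10.9–11.9% | 96.0% | 95.3% |
| 0.20 | 2.00 | 16.6% | 16.4–18.1% | 89.3% | 88.4% |
| 0.30 | 2.50 | 21.5% | 21.8–23.0% | 81.6% | 80.3% |

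The t test on the scores kept its type I error at about 5% throughout. A continuity correction does not rescue the pooled test: its error was still 6.2–7.0% at ICC 0.05 and 19.0–20.1% at 0.30.

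**Step 4. Forces in the other direction.** A clinician who tends to say yes, or no, to every patient gains on one half of the scenarios and loses on the other, so scores vary less than binomial. With a pure tendency of logit SD 1.5, the pooled test's type I error is 2.3%; with SD 2 it is about 1.4%. Scenario difficulty that differs (0.7 in three and 0.3 in three) gives 3.8%.

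Mixtures on the logit scale, all SDs assumed:

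| Skill SD | Tendency SD | Difficulty spread | Pooled test type I error |
|---|---|---|---|
| 0.5 | 1 | ±1 | 4.9% |
| 0.8 | 1.5 | ±1.5 | 4.8% |
| 0.5 | 0 | ±1.5 | 4.3% |
| 0.8 | 1 | ±1 | 8.5% |

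**The case against.** The best defence is that the article never states a pooled analysis. It defines a per-clinician score, words the alternative as means of 4.5 and 3 out of 6, and counts clinicians per group. The power simulations might have compared simulated scores, and step 2 shows that such a comparison can produce 99.2%. This stands as far as it goes: a reader might infer that the figure proves pooling, and it does not. It does not save the plan, because the test actually named is a binomial one and the score-based tests are assigned to the surveys only. The score reading also needs equal accuracy across clinicians.

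A reader might also infer that the P value will be too small. The documents do not support that. The 8–23% comes from an assumed ICC and from skill differences alone. The design has three safe and three unsafe scenarios, and some plausible mixtures leave the error close to 5%. What can be said is that the 5% is not assured.

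Finally, a reader might infer that the trial is underpowered. It is not, over the assumed range: a clinician-level analysis of 50 participants keeps at least about 80% power. The matter cannot simply be left to an unseen analysis plan, because the article itself fixes the test and prints the power figure.

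**Conclusion.** The point holds in this form. The named primary test does not match a design in which the arm is assigned to the clinician and each clinician makes six decisions. The 99.2% is arithmetically sound only if accuracy does not vary between clinicians, whichever unit was used to obtain it.

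With between-clinician variation at an ICC of 0.05–0.30, a valid clinician-level test has about 98% falling to about 80% power. The pooled binomial test would then have a type I error of about 8–23% if skill differences act alone, about 1.4–2.3% if a strong response tendency acts alone, and values between when the two mix. The ICC range and the logit SDs are assumptions. The conclusion that does not depend on them is that the binomial test has no means of adapting to the correlation, while a test based on the observed spread of clinician scores does.

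**What to change.** In Data Collection and Analysis for Simulated Trial, replace the 2-sample binomial test with a comparison of the per-clinician 0–6 score already defined in the Overview. A two-sample t test or a permutation test would do, with the mean difference and its confidence interval reported. A logistic mixed model with a clinician random effect and scenario fixed effects is an alternative.

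In Sample Power for Simulated Trial, state that 99.2% assumes no between-clinician variation, name the test that was simulated, and give power as about 80–98% over an ICC of 0.05–0.30.

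The cost is a few sentences and a less favourable stated power. No participants are added. The article expects evaluation data collection to begin in April 2026, so the change should be made before then.

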#### Study Procedures and Setting

Respondents who meet the eligibility criteria will participate in an informed consent process and complete a short demographic and clinical experience survey. At the time of the scheduled test session, participants will connect via the cloud-based video platform from their homes or a quiet space of their choosing. Each participant will connect with a member of the research team and share their screen as they interact with the prototype. This will allow the visualization of computer mouse movements to show which areas and features of the prototype they are focusing on. After receiving a standardized orientation to the simulated EHR environment, the research team member will begin recording, and the clinicians will open the simulated EHR environment (with or without the ASSIST-ICU CDSS) to begin the study. The fictional patients’ scenarios will be presented in their preassigned random order. After exploring the EHR environment, participants will be asked to respond whether they (1) would or (2) would not decide to move each patient out of bed that day.

#### Data Collection and Analysis for Simulated Trial

Clinicians will receive a score ranging from 0 to 6 based on the number of scenarios answered correctly. Participants will complete 3 brief surveys using a hyperlink in the cloud-based video platform’s chat feature to assess the usability (System Usability Scale [SUS] [55]), cognitive workload (NASA-TLX [43]), and acceptability (Acceptability of Intervention Measure [AIM] [56]) of CDSS and decision-making process as a whole. The SUS is a 10-item Likert-type scale that is widely used to measure usability across a broad range of interfaces and performs well psychometrically (Cronbach α=0.70-0.92) [57,58]. The NASA-TLX is a 6-item scale that measures subjective cognitive workload in performing a specific task and is a reliable measure of cognitive workload across industries, including ICU clinicians (Cronbach α=0.83-0.92) [59]. The AIM is a 4-item Likert-type scale that measures acceptability and performs well psychometrically (Cronbach α=0.85-0.91).

Summary statistics will be calculated for the collected measures by group. Continuous measure distributions will be assessed for normality and reported as means and SDs or medians and IQRs, as appropriate. Categorical measures will be reported as counts and percentages for each level. A 2-sample binomial test will be used to test the null hypothesis that decision accuracy with the support tool does not differ from accuracy without it. Further between-group assessments will be conducted for SUS, NASA-TLX, and AIM scores using 2-sample 2-tailed *t* tests or the Wilcoxon rank sum test. *P* values will be reported based on 2-sided alternatives, and statistical significance will be evaluated at α=.05.

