## Discussion

### Study Significance and Strengths

This study aims to develop and evaluate a CDSS that assists clinicians in coordinating and delivering evidence-based physical activity interventions at the point of care, with minimal extraneous cognitive workload and demonstrated feasibility of real-world trial procedures.

This study rigorously addresses the most common potential pitfalls identified with CDSSs, including usability, increased cognitive workload, usefulness, effectiveness, safety, fragmented workflows, and lack of spread, by using a novel sequence of methods to design and test the CDSS interface [29]. First, we use a UCD approach, considered a gold standard, which involves iterative evaluations with future system users to enable user perspectives to be incorporated into the system design to improve usefulness and usability [46,62-64]. Second, we use the CFIR implementation science framework during the design phase to understand barriers and facilitators to CDSS implementation [44,45]. Next, we conduct a virtual trial to establish the safety and effectiveness of the intervention in a simulated EHR environment before testing the feasibility of CDSS in real-world settings. Although UCD is widely used in health care, randomized tests of efficacy and rigorous testing of CDSSs in a pragmatic trial within a single study are rare. Furthermore, few CDSS studies apply implementation science theories to inform CDSS development and testing; however, designing with an implementation science lens can help identify additional modifiable barriers to address during CDSS design and implementation [65].

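### The simulated trial's pooled 0-6 score cannot by itself support the statement that the trial will establish the tool's safety

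*Protocol article*

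**What the plan says.** The Overview of the simulated trial (Protocol article, Phase 2) sets the scenario mix: "Of the 6 simulations, 3 will meet the out-of-bed safety definition, and 3 will not". Table 2 gives one point for mobilising when the tool recommends it, one point for not mobilising when the tool advises against it, and zero otherwise. The points are added, and "the number of correct decisions (range 0-6) for each participant will serve as our outcome measure of effectiveness". Data Collection and Analysis for Simulated Trial repeats this: "Clinicians will receive a score ranging from 0 to 6 based on the number of scenarios answered correctly". It then names one accuracy test, a two-sample binomial comparison of decision accuracy with and without the tool. The other measures in this trial are the usability, workload and acceptability surveys. No result by scenario type is stated.

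The Discussion (Study Significance and Strengths) gives the purpose: "we conduct a virtual trial to establish the safety and effectiveness of the intervention in a simulated EHR environment", ahead of feasibility testing in real-world settings.

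**The concern.** Missing a chance to mobilise a patient who is ready and mobilising a patient who is not are different errors. Only the second bears on safety. The score gives them equal weight and reports the sum, so a gain on the safe scenarios can offset a loss on the unsafe ones and still yield a positive result.

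At stake is the safety conclusion rather than the validity of the primary test. The simulation is the one stage at which unsafe decisions can be compared between concurrent groups with scenario status known in advance. The later ICU study is a nonrandomized pretest-posttest design that relies on reported safety events. If the simulation reports only the total, it leaves unanswered the safety question that the Discussion assigns to it.

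**Working it through.** **Inputs from the Protocol article**
- Scenarios: 3 safe and 3 unsafe per clinician (Overview).
- Intervention mean: "Assuming a true mean of 4.5 correct decisions out of 6 simulations (75% probability) when using the decision tool" (Sample Power for Simulated Trial).
- Control mean: "3 correct decisions (50% probability) when not using it" (same section).
- Size and power: "25 clinicians per group will provide 99.2% power when testing for a between-group difference at α=.05" (same section).
- Sidedness: "values will be reported based on 2-sided alternatives, and statistical significance will be evaluated at α=.05" (analysis section).

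This gives 25 × 6 = 150 decisions per arm, of which 25 × 3 = 75 are safe and 75 unsafe.

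**1. The plan's own power figure.** Take 75% against 50% on 150 decisions per arm, two-sided 0.05, decisions independent. Power = Φ[(0.25 − 1.96·√(2·0.625·0.375/150)) / √((0.75·0.25 + 0.50·0.50)/150)] = 99.5%. Exact enumeration gives 99.3% with a continuity correction and 99.3% with the Fisher exact test. The stated 99.2% is reproduced, and it counts all 150 decisions. With only 25 binary outcomes per arm, power would be 44%.

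**2. What the planned means fix.** Let *s* be the probability of a correct decision in a safe scenario and *u* that in an unsafe one. The mean score is 3(*s* + *u*). The planned means therefore give *s* + *u* = 1.0 in control and 1.5 in the intervention arm. The individual values are not given, so every split below is an assumption.

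**3. When unsafe mobilisation can rise at the full planned effect.** Unsafe mobilisation is 1 − *u*. With *u*(control) = 1.0 − *s*(control) and *u*(tool) = 1.5 − *s*(tool), it rises when *s*(tool) > *s*(control) + 0.5. Because *s*(tool) cannot exceed 1, control accuracy on safe scenarios must be below 50%.

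**4. Range of assumed splits.** Power to declare benefit uses the exact distribution of the total, Binomial(75, *s*) + Binomial(75, *u*), with the continuity-corrected test and independent decisions.

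| Control *s* / *u* | Tool *s* / *u* | Mean scores | Unsafe mobilisation | Power |
|---|---|---|---|---|
| 50% / 50% | 75% / 75% | 3.0, 4.5 | 50% to 25% | 99.3% |
| 33% / 67% | 100% / 50% | 3.0, 4.5 | 33% to 50% | 99.7% |
| 30% / 70% | 95% / 55% | 3.0, 4.5 | 30% to 45% | 99.7% |
| 40% / 60% | 100% / 50% | 3.0, 4.5 | 40% to 50% | 99.7% |
| 50% / 50% | 100% / 50% | 3.0, 4.5 | 50%, no change | 99.7% |
| 50% / 50% | 100% / 40% | 3.0, 4.2 | 50% to 60% | 95% |

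The second row in scenarios per clinician: control 1.0 + 2.0 = 3.0; tool 3.0 + 1.5 = 4.5. The fifth row is the limit when control is even: the full effect leaves no room for a rise. The sixth row shows that a significant result short of the planned effect does.

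**5. A uniform shift to *yes*.** If every scenario is mobilised with the same higher probability, the gain on three safe scenarios equals the loss on three unsafe ones. Mobilising everyone scores 3 + 0 = 3.0, the assumed control mean. Such a shift does not raise the score.

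**6. Precision on unsafe scenarios alone.** The 95% half-width of the arm difference is 1.96·√(2*p*(1 − *p*)/75): 0.15 at *p* = 0.33 and 0.16 at *p* = 0.50, before clustering within clinician.

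**The case against.** The strongest defence is that the balanced set already guards against indiscriminate mobilising: as step 5 shows, a uniform shift to *yes* earns nothing, and the total rises only if clinicians discriminate better overall. That stands, and it limits the problem to a large gain on safe scenarios combined with a smaller loss on unsafe ones.

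A reader might infer that more unsafe mobilisation is a likely side effect of the tool. The documents do not support that. The algorithm section describes an icon showing readiness as yes or no with the reasons behind it, so in an unsafe scenario the clinician sees *no*. Mobilisation would have to exceed that of controls who see no advice at all, through override or misreading. The Conceptual Framework does accept that a poor design can impair interpretation, so the possibility is not fanciful.

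A reader might also infer that the score is a formal safety gate before ICU use. No section sets a go/no-go rule; the Overview calls the score a measure of effectiveness, and the safety purpose rests on one Discussion sentence. Falls, unplanned extubations and line removals are tracked in the ICU study.

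Finally, secondary breakdowns may sit in a fuller document, and the general line about reporting categorical measures as counts and percentages does not exclude a split. It does not commit to one either. The point here is narrower: the stated outcome and the stated safety purpose do not match.

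**Conclusion.** The point holds as a mismatch between outcome and claim. The primary test remains a valid comparison of overall accuracy, but a positive result would not in itself show that the tool is safe.

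At the full planned effect, masking of a rise in unsafe mobilisation requires control accuracy below 50% on safe scenarios. The Background figure of 29% of patients receiving activity beyond active range of motion makes a cautious control group plausible, but it is not an input to this trial. With an even control group, only a result short of the planned effect can hide a rise.

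The power figures treat decisions as independent, as the plan's own figure appears to. Clustering within clinician would alter them but not the masking. Even with the scenarios split, a half-width of about 15 to 16 points is too wide to establish safety in any strong sense.

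**What to change.** Keep the 0-6 score, the sample size and the primary test. Name as a key secondary outcome the number of the three unsafe scenarios in which the clinician chose to mobilise, reported by arm with the difference and a confidence interval that allows for clustering within clinician. Report the three safe scenarios in the same way.

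Base any safety statement on that interval, not on the direction of the point estimate. With 75 decisions per arm, a rule that fails the tool whenever the observed unsafe-mobilisation rate is higher than in control would fail a tool with no true effect about 47% of the time (exact binomial, *p* = 0.33 or 0.50, independent decisions).

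Reword the Discussion sentence so that the safety claim matches the precision available, for example by saying that the virtual trial will estimate the effect on unsafe mobilisation decisions.

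The cost is two extra summary lines from decisions already recorded, and a more modest safety claim. No further participants are needed.
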